|                                  |                                                                                                                                                                                                                                                                                                                                                                                                                                                                                                                                                                                                                                                                                                                                                                                                                                                                                                                                                                                                                                                                                                                                                                                                                                                                                                                                                                                                                                                                                                                                                                                                                                                                                                                                                                                                                                                                                                                                                                                                                                                                                                                                                 |
|----------------------------------|-------------------------------------------------------------------------------------------------------------------------------------------------------------------------------------------------------------------------------------------------------------------------------------------------------------------------------------------------------------------------------------------------------------------------------------------------------------------------------------------------------------------------------------------------------------------------------------------------------------------------------------------------------------------------------------------------------------------------------------------------------------------------------------------------------------------------------------------------------------------------------------------------------------------------------------------------------------------------------------------------------------------------------------------------------------------------------------------------------------------------------------------------------------------------------------------------------------------------------------------------------------------------------------------------------------------------------------------------------------------------------------------------------------------------------------------------------------------------------------------------------------------------------------------------------------------------------------------------------------------------------------------------------------------------------------------------------------------------------------------------------------------------------------------------------------------------------------------------------------------------------------------------------------------------------------------------------------------------------------------------------------------------------------------------------------------------------------------------------------------------------------------------|
|                                  | 
Secondary endpoints
 
MaaT033 best dose regimen will be evaluated based on different evaluation:
 
 
- Overall safety will be evaluated from V1 to V4. All AEs will be evaluated by the safety committee.
 
- The product activity:
 
 
Definition of activity1 is here described by the evaluation of the microbiota modification: the proportion and number of different OTUs that colonize the gastro-intestinal tract of the patients. Assessment will be calculated using an alpha-diversity index (i.e. Richness, Shannon, Simpson or other ecology indexes).
 
Definition of activity2 is here described by the IMP bacterial engraftment: the percentage of bacteria that colonize the gastro-intestinal tract of the patients and come from MaaT033, as compared to baseline (visit1). Assessment will be calculated using Operational Taxonomic Units (OTUs) or a beta-diversity index (i.e. UniFrac, Jaccard, Bray-Curtis or other ecology indexes).
 
Activities1&2 will be assessed at V2, V3 and V4, as compared to the baseline V1.
 
 
- Patient compliance:
 
 
Based on the level of compliance of the different cohorts evaluated with a daily follow up using a diary, the best dose regimen in terms of activity may be re-considered. A compliance under 60% for a patient would not be considered acceptable to validate the corresponding dose regimen.
 
Exploratory endpoints: Evaluation of MaaT033's impact on patients' gut colonization
 
Examination at, and evolution from V1 to V4, of the composition of the intestinal microbiota
 
Analysis includes but is not limited to the evaluation of the microbiota modification, based on diversity, and the richness index – using 16S and/or shotgun next generation sequencing (NGS) technology
 
Examination of gut inflammation markers (stool, blood)
 
Based on molecular analyses, description of gut resistome carriage from V1 to V4
 |
| NUMBER OF SUBJECTS        | 
The enrollment into the study will continue until a maximum of 27 subjects are treated with MaaT033 and evaluable, based on the step-up and safety process:
 
27 patients – 5 cohorts
                                                                                                                                                                                                                                                                                                                                                                                                                                                                                                                                                                                                                                                                                                                                                                                                                                                                                                                                                                                                                                                                                                                                                                                                                                                                                                                                                                                                                                                                                                                                                                                                                                                                                                                                                                                                                                                                                                                                        |
| ESTIMATED NUMBER OF SITES | 3-4 in France                                                                                                                                                                                                                                                                                                                                                                                                                                                                                                                                                                                                                                                                                                                                                                                                                                                                                                                                                                                                                                                                                                                                                                                                                                                                                                                                                                                                                                                                                                                                                                                                                                                                                                                                                                                                                                                                                                                                                                                                                                                                                                                            |
| STUDY TREATMENT           | Route of administration: oral                                                                                                                                                                                                                                                                                                                                                                                                                                                                                                                                                                                                                                                                                                                                                                                                                                                                                                                                                                                                                                                                                                                                                                                                                                                                                                                                                                                                                                                                                                                                                                                                                                                                                                                                                                                                                                                                                                                                                                                                                                                                                                                   |

|                                                                                   |                    |                                                                      |
|-----------------------------------------------------------------------------------|--------------------|----------------------------------------------------------------------|
| [figure not shown] | DOCUMENT    | Protocol ID : MPOH05
EudraCT N° : 2019-004253-89
Version: 10.0 |
|                                                                                   | CIMON STUDY | Date : 04 MAY 2021
Page 13 / 70                                   |

|                                                   |                                                                                                                                                                                                                                                                                                                                                                                                                                                                                                                                                                                                                                                                                                                                                                                                                             |
|---------------------------------------------------|-----------------------------------------------------------------------------------------------------------------------------------------------------------------------------------------------------------------------------------------------------------------------------------------------------------------------------------------------------------------------------------------------------------------------------------------------------------------------------------------------------------------------------------------------------------------------------------------------------------------------------------------------------------------------------------------------------------------------------------------------------------------------------------------------------------------------------|
|                                                   | 
After recovering from neutropenia (neutropenia is defined as Poly-Nuclear Neutrophils count <math>\leq 0.5 \times 10^9</math> cells/L)
 
Dose regimen:
 
 
- Cohort 1 (3 patients): 1 capsule (per os) at day1 and at day7, e.g., on a Tuesday and the Monday of the following week. Step up of dose regimen will then be as follows:
 
- Cohort 2 (6 patients): 1 capsule/day (corresponding to a maximum of 7 capsules) – 7 days (period of treatment)
 
- Cohort 3 (6 patients): 3 capsules/day (corresponding to a maximum of 21 capsules) – 7 days
 
- Cohort 4 (6patients): 3 capsules/day (corresponding to a maximum of 42 capsules) – 14 days
 
- 9 capsules/day (corresponding to a maximum of 63 capsules) – 7 days
 
 |
| ASSESSMENT/
SCHEDULE                   | 
Estimated inclusion period: 5 to 7 months
 
Calculated total duration of the study from start to last patient last visit: 7 to 9 months
                                                                                                                                                                                                                                                                                                                                                                                                                                                                                                                                                                                                                                                                         |
| DURATION OF STUDY
PERIOD (per Subject) | 
Participation period for a patient:
 
Total potential duration: up to 6-7 weeks
                                                                                                                                                                                                                                                                                                                                                                                                                                                                                                                                                                                                                                                                                                                          |

|                                                                                   |             |                                                                                                            |
|-----------------------------------------------------------------------------------|-------------|------------------------------------------------------------------------------------------------------------|
| [figure not shown] | DOCUMENT    | Protocol ID : MPOH05
EudraCT N° : 2019-004253-89
Version: 10.0
Date : 04 MAY 2021
Page 14 / 70 |
|                                                                                   | CIMON STUDY |                                                                                                            |

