| STUDY OBJECTIVES        | 
Primary:
Evaluation of maximal tolerable dose of MaaT033 in patients with AML or HR-MSD
 
Secondary:
Evaluation of overall safety
Dose regimen evaluation: identification of a recommended phase II dose (RP2D) based on gut microbiota engraftment
 
Exploratory:
                                                                                                                                                                                                                                                                                                                                                                                                                                                                                                                                                                                                                                                                                                                                                                                                                                                                                                                                                                                                                                                                                                                                                                                                                                |

|                                                                                   |                    |                                                                      |
|-----------------------------------------------------------------------------------|--------------------|----------------------------------------------------------------------|
| [figure not shown] | DOCUMENT    | Protocol ID : MPOH05
EudraCT N° : 2019-004253-89
Version: 10.0 |
|                                                                                   | CIMON STUDY | Date : 04 MAY 2021
Page 11 / 70                                   |

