### 8.2 STUDY DESIGN

#### 8.2.1 **Methodology and study phases**

Open-label, single-arm phase 1 study to evaluate the safety of MaaT033 in a step-up dosing design from 2 capsules 7 days apart to 9 capsules per day for 7 days.

Choice of cohort is based on the definition of maximum and minimum dose regimen acceptable for good compliance. 1 capsule per week is a reasonable minimum dosing while 9 capsules per day is a maximum we could define for such a population, already having quite important medications.

Our target dose is also in between these 2 cohorts, with 3 capsules per day. We decided to assess the impact of treatment duration with the comparison between a 7 days courses versus 14 days.

The study has the following phases:

- **Patient pre-screening phase** - Patients diagnosed with hematologic malignancy will be asked if they are willing to participate in this study by the investigating physician and will sign the informed consent form before any study examination. Only patients with neutropenia recovery will be finally included in the study.  
Neutropenia recovery is defined as a level of Absolute Neutrophil Count (ANC)  $\geq 0.5 \times 10^9$  cells/L.
- **Treatment phase** - The treatment will be started within 2 days after patient's inclusion. Clinical evaluation will be performed at baseline, at the interim visit (day7), before new cycle of chemotherapy start if any (day19 if not) and after new cycle chemotherapy if any (day44 if not). A step-up process will be applied between 5 different cohorts of patients and will depend on patient's tolerance of the treatment.
- **Follow-up phase:**  
Patient's overall status will be evaluated at D44 post inclusion (V4).  
AE/SAE collection will be performed from time of informed consent to V4.

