#### **8.3.2 Secondary endpoint: Dose regimen evaluation**

MaaT033 best dose regimen will be evaluated based on different evaluations:

- Overall safety will be evaluated from V1 to V4. All AEs will be evaluated by the safety committee.
- The product activity:

Definition of activity1 is here described by the evaluation of the microbiota modification: the proportion and number of different OTUs that colonize the gastro-intestinal tract of the patients. Assessment will be calculated using an alpha-diversity index (*i.e.* Richness, Shannon, Simpson or other ecology indexes).

Definition of activity2 is here described by the IMP bacterial engraftment: the percentage of bacteria that colonize the gastro-intestinal tract of the patients and come from MaaT033, as compared to baseline (visit1). Assessment will be calculated using Operational Taxonomic Units (OTUs) or a beta-diversity index (*i.e.* UniFrac, Jaccard, Bray-Curtis or other ecology indexes).

Activities1&2 will be assessed at V1, V2, V3 and V4.

- Patient compliance: Based on the level of compliance of the different cohorts evaluated with a daily follow up using a diary, the best dose regimen in terms of activity may be re-considered. For a patient, a compliance of less than 60% of capsules that were supposed to be ingested would not be considered acceptable to validate the corresponding dose regimen.

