#### **12.1.4.1 Tolerability consideration:**

Investigators will be trained regarding the mode of action of the investigational medicinal product and to be particularly attentive to any signs of toxicity.

**Dose Limiting Toxicity (DLT):** Based on the literature and our preclinical data, no particular toxicity is expected. Toxicity events will be defined as any at least possibly related adverse event grade  $\geq 3$  based on CTCAE v5.0 criteria. Due to the specific therapeutic protocol that blood cancer patients usually follow, the follow-up of patients in term of DLT is set from V1 (end of neutropenia) to V3 (start of a new chemotherapy cycle, or consolidation). Nevertheless, there are some anatomical or physiological system events that will be considered as expected in the context of patients with AML or HR-MSD, and thus not related to the treatment. Such events will only be considered DLT when grade  $> 3$ :

- Blood and lymphatic system disorders (DLT when grade 4 or 5)
- Immune system disorders (DLT when grade 4 or 5)

Depending on the number of DLTs, the dose is either escalated (0 DLTs) or de-escalated ( $\geq 2$  DLTs). Due to our specific drug activity assessment goals, cohorts 2 to 5 will systematically be expanded with 3 extra patients (0 or 1 DLTs) each.

|                                                                                   |                    |                                                                      |
|-----------------------------------------------------------------------------------|--------------------|----------------------------------------------------------------------|
| [figure not shown] | DOCUMENT    | Protocol ID : MPOH05
EudraCT N° : 2019-004253-89
Version: 10.0 |
|                                                                                   | CIMON STUDY | Date : 04 MAY 2021
Page 49 / 70                                   |

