#### 14.1.1 **Endpoints**

Detailed definitions of endpoints are given in [section 8.3.1](#).

The primary evaluation criterion is the proportion of patients having experienced drug related adverse events for the determination of a recommended phase 2 dose (RP2D).

Secondary endpoints are:

- Evaluation of microbiota reconstitution post MaaT033
  - Alpha-diversity: Simpson index, Shannon index, Richness index
  - Similarities between samples: Bray-Curtis/Jaccard/UniFrac distances indexes, Sorensen index, Pearson index, Spearman index
- Duration of overall response on the hematologic malignancy (blasts)
- Compliance to allogeneic MaaT033 treatment
- Acceptability of MaaT033 by the patient
- Number of patients receiving the full treatments
- Evaluation of MaaT033 activity and/or impact on:
  - Number and percentage of patients having experienced at least one infection requiring antibiotic/antiviral/antifungal therapy after MaaT033 treatment start
  - Number and percentage of patients having experienced at least one microbiologically documented infection requiring antibiotic/antiviral/antifungal therapy after MaaT033 treatment start
  - Events potentially related to GI infection (fever, diarrhea, abdominal pain, bloating)
  - Fecal resistome and MDRB carriage
  - Evaluation of stools: Bristol stool chart

Exploratory endpoints encompass

- Assessment of a microbiota signature
- Impact of MaaT033 on the immune system

The final main analysis will be performed when all enrolled patients have completed treatment and follow-up period (28 days). Complementary analysis on safety and 12 months' survival follow up will be updated when all patients have had the opportunity to be followed for 12 months.

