### 14.3.5 Analysis of the main criterion

The number and percentage of patients having experienced AEs between V1 and V4 will be described. Relation of AEs to the drug treatment will be assessed by the safety committee in a final review. The committee will then provide a conclusive decision on MaaT033 safety.

|                                                                                   |                    |                                                                      |
|-----------------------------------------------------------------------------------|--------------------|----------------------------------------------------------------------|
| [figure not shown] | DOCUMENT    | Protocol ID : MPOH05
EudraCT N° : 2019-004253-89
Version: 10.0 |
|                                                                                   | CIMON STUDY | Date : 04 MAY 2021
Page 54 / 70                                   |

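### Overall safety, the AE percentage in 14.3.5 and the infection endpoints mix the capsule period with a later, conditional chemotherapy cycle, and 14.3.5 conflicts with the V1–V3 primary window

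*Protocol*

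**What the plan says.** The Synopsis and 7.2 list "Evaluation of overall safety" as a secondary objective. Section 8.3.2 makes it one of the evaluations behind the best dose regimen and sets its window: "Overall safety will be evaluated from V1 to V4. All AEs will be evaluated by the safety committee". Section 12.1.4.3 lets the committee draw on all available safety data when it selects the RP2D.

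Section 14.3.5, on the main criterion, states: "The number and percentage of patients having experienced AEs between V1 and V4 will be described". As worded, that count carries no grade or relatedness condition. Relatedness follows in a separate sentence, as a final committee review.

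Among the secondary endpoints, 14.1.1 lists "Number and percentage of patients having experienced at least one infection requiring antibiotic/antiviral/antifungal therapy after MaaT033 treatment start", and a second endpoint of the same form for microbiologically documented infections. Neither has a stated end, a split by period or a relatedness condition.

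The visit schedule places a chemotherapy cycle between V3 and V4, but only conditionally. Under 8.2.1, evaluations take place "before new cycle of chemotherapy start if any (day19 if not) and after new cycle chemotherapy if any (day44 if not"). By contrast, the primary endpoint in 8.3.1 runs from visit 1 to visit 3. Section 12.1.4.1 explains why: given the usual treatment course of these patients, follow-up "in term of DLT is set from V1 (end of neutropenia) to V3 (start of a new chemotherapy cycle, or consolidation").

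**The concern.** Capsules are taken for 7 or 14 days. A patient who goes on to consolidation or another cycle then has intensive chemotherapy between V3 and V4. A percentage of patients with at least one AE, or at least one infection, from treatment start onward cannot show whether the event came before or during that cycle.

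Two things can go wrong when regimens are set side by side. If most patients in every cohort receive the cycle, its events push all cohorts towards the same high percentage, and a difference that arose in the capsule period shrinks. If cohorts differ by chance in how many of their 6 patients receive the cycle, a difference appears with no product effect. Infections and GI disorders, the events of special interest in 12.1.3.3, are plausibly the most exposed.

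The protocol recognises the issue for DLTs but does not carry the reasoning over to these summaries. Moreover, the V1–V4 window stands in the analysis section for the main criterion, where it contradicts the endpoint definition.

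**Working it through.** **Inputs from the protocol.** V1 is D1; V3 is D19 (D14–D24); V4 is D44 (D34–D54) (sections 4 and 11). Capsules last 7 or 14 days (11.4.3). Cohorts 2–5 have 6 patients each (8.2.2). The protocol gives no AE or infection rate for either period and no expected share of patients with a next cycle, so it offers no figure of its own to reproduce on this point.

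**Step 1: windows side by side.**

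| Item | Section | Start | End |
|---|---|---|---|
| Primary endpoint | 8.3.1 | V1 | V3 |
| DLT follow-up | 12.1.4.1 | V1 | V3 |
| Analysis of the main criterion | 14.3.5 | V1 | V4 |
| Overall safety | 8.3.2 | V1 | V4 |
| Infection endpoints | 14.1.1 | treatment start | not stated |

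Rows 1 and 3 concern the same criterion and disagree.

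**Step 2: share of follow-up after V3**, (V4 − V3)/(V4 − 1):
- nominal (D19, D44): 25/43 = 58%
- smallest (D24, D34): 10/33 = 30%
- largest (D14, D54): 40/53 = 75%

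**Step 3: dilution, on assumed rates.** Let p be the risk of at least one event before V3, q the added risk from the next cycle, and f the share of patients receiving it, with independent periods. The V1–V4 risk is 1 − (1 − p)(1 − qf), so a true difference in p is multiplied by (1 − qf). With f = 1 and p = 10% versus 30% (20 points):
- q = 30%: 37% vs 51%, 14 points
- q = 50%: 55% vs 65%, 10 points
- q = 70%: 73% vs 79%, 6 points

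A second assumed set, p = 20% versus 50% with q = 50%, 70% or 90%, shrinks 30 points to 15, 9 or 3.

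**Step 4: imbalance, on assumed rates.** Take p = 10% in both cohorts, so there is no product effect. The gap is (1 − p) × q × (difference in f).

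| q | 3/6 get cycle | 5/6 | 6/6 | Gap 6/6 − 3/6 | Gap 6/6 − 5/6 |
|---|---|---|---|---|---|
| 30% | 23.5% | 32.5% | 37% | 13.5 points | 4.5 points |
| 50% | 32.5% | 47.5% | 55% | 22.5 points | 7.5 points |
| 70% | 41.5% | 62.5% | 73% | 31.5 points | 10.5 points |

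Counted only to V3, every gap is zero. A variant with p = 20%, a 20% post-V3 risk without a cycle, and 50%, 70% or 90% with one gives 60% vs 48%, 76% vs 56% and 92% vs 64% for 6/6 versus 3/6, that is 12, 20 or 28 points.

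**Scale.** One patient in a cohort of 6 is 1/6 = 16.7 points, so the 6/6 versus 3/6 gaps amount to roughly one or two patients.

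**The case against.** The strongest reply has four parts.

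**Tabulation belongs in the statistical analysis plan.** Section 14.3.6 leaves secondary analyses descriptive unless that plan says otherwise, and a split by period may be there. This holds for the layout of tables. It does not hold for the windows, which the protocol itself fixes in 8.3.2 and 14.3.5, nor for the conflict between 14.3.5 and 8.3.1.

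**The decisive safety rules are protected.** This stands. Escalation and the MTD use related DLTs counted no later than V3 (8.2.2, 12.1.4.1, 12.1.4.2), and the RP2D objective refers to engraftment. A reader might infer that dose escalation is distorted; the protocol does not support that.

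**The committee judges relatedness.** This is a real safeguard for AEs, and 8.3.2 sends all AEs to the committee. It is not part of the infection endpoints as written, nor of the count in 14.3.5.

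**Following patients through the cycle is reasonable.** This also stands. Section 14.1.1 places the infection endpoints under product activity or impact, 6.1.2 names bloodstream infection as a risk to be contained, and 6.5.4 cites deaths from resistant bacteria translocated from another FMT product. A later infection may therefore be product harm or a failure of intended activity. A reader might conclude that only pre-cycle events should inform the regimen choice; the protocol gives no basis for discarding the later ones.

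In addition, eligibility favours patients likely to receive the next cycle (9.1), so a 3/6 versus 6/6 split is a deliberately wide contrast. Common dilution may matter more than imbalance.

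**Conclusion.** The concern holds for the descriptive safety summaries and for the wording of 14.3.5. At nominal visits 58% of follow-up (30% to 75% over the windows) lies after V3, where a conditional chemotherapy cycle takes place. Overall safety, the AE percentage and the infection endpoints all run across that point without a stated split. Section 14.3.5 also contradicts 8.3.1 on the window of the main criterion.

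It is tempting to say that chemotherapy events swamp the capsule period. The protocol contains no rates that would show this. The 3- to 15-point residual differences and the 4.5- to 31.5-point spurious gaps rest entirely on assumed risks, on independence between periods and on chosen shares receiving the cycle. They show that dilution or distortion is possible, not how large it will be. It would likewise be an inference to say that the infection endpoints end at V4. AE collection stops there (8.2.1), but 14.1.1 also mentions a 28-day follow-up and 12-month updates, so the end is simply not fixed. The matter should be corrected; it does not put the escalation scheme in doubt.

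**What to change.** 1. In 14.3.5, align the analysis of the main criterion with the V1–V3 window of 8.3.1, and present the V1–V4 AE description as overall safety.
2. In 14.1.1, state when the infection endpoints end.
3. In 8.3.2 and 14.3.6, tabulate AEs, SAEs and infections per regimen for (a) first capsule to the start of the next chemotherapy cycle, or to V3 if there is none, and (b) from then to V4, split by whether a cycle was given. Keep the V1–V4 total alongside.
4. Show the committee all periods when it selects the RP2D, rather than restricting the safety comparison to period (a).

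No new data are needed: 12.1.3.1 already requires AE onset dates, visits are dated, and treatments given during the study are recorded in the eCRF. The cost is some wording and one extra set of tables. With at most 6 evaluable patients per planned cohort, and fewer once period (b) is split, the cells will be small and should be read as description only.
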